## 5. Statistical methods

152 

### 5.1 Sample size and power

153

154 The sample size calculation is based on evaluation of the primary objectives. For evaluation of  
 155 superiority, it is assumed that 13% of patients who undergo GBP will have substantial adverse events  
 156 (as defined in the Study outcomes) over 5 years. It is further assumed that this risk is 35% lower in  
 157 patients in the SG group. Based on these assumptions, it is estimated that a total of 2100 patients  
 158 (1050 in each group) will be required to detect a difference in time to substantial adverse event with  
 159 >90% power at two-sided 2.5% significance level using Cox proportional hazards regression model.

160 Initially the power calculation was based on a SAE rate of 5% over 5 years, leading to the need to  
 161 include 4000 patients (especially regarding subgroup analysis). Partly due to slower than expected  
 162 inclusion rate, but mainly based on data suggesting more events of substantial adverse events than  
 163 expected (i.e., 13%) the sample size was recalculated to n=2100 to obtain sufficient power.

164 This sample size will also have 90% power to evaluate non-inferiority of 5 % weight loss difference  
 165 over 5 years between the two groups, assuming 15 kg standard deviation in weight loss over follow-  
 166 up with two-sided 2.5% significance level.

167

168 See appendix for an updated, post hoc, power-calculation before the closure of the trial inclusion.

169

170 

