## 3. Study Design

### 3.1 Overview

This is a randomized, Scandinavian multi-centre study comparing the two most abundant bariatric surgery techniques worldwide; laparoscopic gastric bypass (GBP) and laparoscopic sleeve gastrectomy (SG). Study design is parallel group study with 1:1 allocation between GBP and SG.

To be invited to participate in the study as a collaborating centre, the operating bariatric clinic has to perform at least 100 bariatric surgeries annually, report to the Scandinavian Obesity Surgery Registry (SOREg) and be able to meet all criteria set in the project plan. The study, to be conducted at approximately 20 bariatric surgery clinics in Sweden and Norway, will include 2100 obese patients approved for bariatric surgery (1050 patients to be operated with SG and 1050 with GBP).

89 The follow-up time for the primary objectives is 5-years.

90

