### 5.2 Principles of analysis

171

172 The primary conclusions from this study will be based on analyses conducted under the principle of  
 173 intention-to-treat. Thus, all randomised patients, with exception to those who withdraw their  
 174 consent, will be included in the analyses. In the analysis, it is further assumed that all randomised  
 175 patients receive the treatment they were randomised to.

Those patients who are randomised but withdraw their consent to use their data will not be included in any analyses. Only the information that they were enrolled into the study and withdrew their consent, and the original treatment group to which they were allocated, will be reported.

Data from all operating clinics (centres) will be pooled in primary analyses. The study will be conducted under a common protocol for each participating clinic with the intention to pool the data for analyses.

In addition to the primary analysis using intention-to-treat population, exploratory analyses using per-protocol (as treated) populations will be conducted for all outcome variables.

For primary outcomes, two-sided 2.5% significance level will be used to identify statistically significant results. The corresponding confidence intervals to be reported will be 97.5% confidence intervals. The use of 2.5% significance is due to two primary endpoints.

There will not be any formal interim analyses on primary outcomes. The safety and Data Monitoring Committee has a responsibility to monitor adverse events and complications during the study follow-up period.

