Taking information above into account and in the interest of not prolonging inclusion period unnecessarily the trial steering committee took a decision to stop inclusion in BEST during spring 2022 (final date 31st of March). At termination of inclusion the number of participants that had been included and operated in BEST were 1752. The trial DSMC reviewed and supported the decision before termination of recruitment to the BEST trial.

1

2

3 Statistical analysis plan for:

4

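### SAP 3.1 and 5.1 state 2100 patients and >90% power for the safety co-primary, but the stated inputs give about 84-88% at 2100 and 76-81% at the 1752 enrolled, and no section gives the safety power at 1752

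*Combined protocol and SAP*

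**What the plan says.** All references are to SAP version 5 unless noted.

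- Section 3.1 gives the trial size as a plan still to be met: the study is to "include 2100 obese patients approved for bariatric surgery (1050 patients to be operated with SG and 1050 with GBP").
- Section 5.1 sets the safety inputs. On gastric bypass (GBP), "it is assumed that 13% of patients who undergo GBP will have substantial adverse events" over five years. On sleeve gastrectomy (SG), "It is further assumed that this risk is 35% lower in" that group. It concludes: "Based on these assumptions, it is estimated that a total of 2100 patients", 1050 per group, will be required, with ">90% power at two-sided 2.5% significance level using Cox proportional hazards regression model". It adds that 2100 replaced a target of 4000 that rested on a 5% rate. Its last line sends the reader to the appendix for an updated power calculation.
- Section 5.2 explains the significance level: "The use of 2.5% significance is due to two primary endpoints". No 5% level is set for a primary outcome.
- The appendix says the event risk is now thought to exceed 25%. It reports 87.5% power for 25% v 16.25% with 413 per group, and explains why recruitment was stopped. It records: "At termination of inclusion the number of participants that had been included and operated in BEST were 1752". It also says that the monitoring committee supported the decision.
- The separate perioperative analysis plan already gives 1752 (its section 3.1), but its section 5.1 sends readers to SAP version 5 for sample size and power.

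**The concern.** The main text describes a trial of a size that was not enrolled and attaches a power figure to it. Two questions follow. Do the stated inputs give the stated power, at 2100 or at 1752? If not, does the appendix supply the missing figure?

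The safety comparison is one of two co-primary outcomes. If SG shows no significant advantage, section 5.1 invites the reading that a trial with more than 90% power at a 13% rate found nothing. How much weight a null result can bear depends on the power of the patients actually enrolled, at the significance level actually used, and on how that power changes with the event rate.

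**Working it through.** **Inputs.** GBP risk p1 = 0.13 and a 35% reduction, so SG risk p2 = 0.65 × 0.13 = 0.0845 (5.1). Two-sided 2.5%, Cox model (5.1). 1050 per group planned (3.1, 5.1). 1752 enrolled (appendix), taken as 876 per group; the equal split is my assumption. No loss to follow-up, because section 5.4 expects near-complete register coverage of events. Section 5.1 does not say whether 35% is a reduction in hazard or in five-year risk, so both are run:
- hazard reading: HR = 0.65, |ln HR| = 0.4308
- risk reading: HR = ln(1 − 0.0845)/ln(1 − 0.13) = 0.634, |ln HR| = 0.4558

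**Formulas.** Events D = n per group × (p1 + p2). Schoenfeld power = Φ(√(D/4) × |ln HR| − z), with z = 2.241 at two-sided 2.5% and 1.960 at two-sided 5%. The comparison of two proportions uses the pooled variance under the null and the unpooled variance under the alternative.

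**Step 1: the plan's own figure at 2100.** D = 1050 × 0.2145 = 225.2.
- HR 0.65: 7.504 × 0.4308 = 3.232; 3.232 − 2.241 = 0.991; power 83.9%.
- HR 0.634: 3.420 − 2.241 = 1.179; power 88.1%.
- Two proportions: 87.1%.

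None exceeds 90%. By Schoenfeld, 90% power needs 268 events (HR 0.65) or 239 (HR 0.634). That is 2 × 268/0.2145 = 2499 or 2 × 239/0.2145 = 2228 patients. At two-sided 5% with HR 0.65, the need is 227 events, or 2 × 227/0.2145 = 2117 patients, and 2100 patients give 89.8%. That is the setting in which 2100 goes with 90%.

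**Step 2: the enrolled 1752 at 13%.** D = 876 × 0.2145 = 187.9.

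| Method | Two-sided 2.5% | Two-sided 5% |
|---|---|---|
| Schoenfeld, HR 0.65 | 76.2% | 84.0% |
| Schoenfeld, HR 0.634 | 81.1% | 87.8% |
| Two proportions | 79.9% | 86.9% |

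Freedman's formula is slightly lower: 74.7% and 79.7% at two-sided 2.5% for the two HRs. Only the 2.5% column is the plan's own level. The 5% column shows that a more lenient level would not restore 90%.

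**Step 3: the appendix figure.** With 413 per group and 25% v 16.25%, the mean risk is 0.20625 and √413 × 0.0875 = 1.778.
- Two-sided 5%: (1.778 − 1.960 × 0.5722)/0.5689 = 1.154; power 87.6%, which matches the stated 87.5%.
- Two-sided 2.5%: (1.778 − 2.241 × 0.5722)/0.5689 = 0.871; power 80.8%.

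The 413 is derived in the appendix as 1031 × 0.80/2, from two-year weight data with 20% further loss. It is not a count for a register-based event outcome.

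**Step 4: the enrolled 1752 at other rates (two-sided 2.5%, 35% lower).**
- 25%: D = 876 × 0.4125 = 361. Schoenfeld 96.8% (HR 0.65) or 99.1% (HR 0.616, from the risks); two proportions 98.9%.
- About 90% is reached at a GBP rate of 16-16.5% on the risk reading (Schoenfeld 89.9% at 16%; two proportions 90.1% at 16.5%). On the hazard reading it is reached at about 18.5% (90.0%).

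**The case against.** The best defence is that the SAP does update itself. Section 5.1 points to the appendix, which replaces 13% with 25%, explains the pandemic's effect on recruitment, gives a new power figure, states 1752 and records the monitoring committee's support. Keeping the planned calculation in the body and the update in an appendix is a layout choice. Testing 1752 against 13% also tests it against a rate the plan no longer relies on; at 25% the enrolled trial is well above 90%.

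Most of that stands, and it rules out three stronger readings:

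- A reader might infer that the trial is underpowered for safety. The documents do not support this, since power at 1752 and 25% is about 97-99%. Even with 20% loss (about 700 per group) it is 92-97%.
- A reader might infer that stopping at 1752 caused the shortfall against 90%. It costs about 7 to 8 points at 13% (83.9% to 76.2%, or 88.1% to 81.1%), but 2100 already misses the stated figure at the stated level.
- A reader might infer that 5.1 was left with no update. The pointer to the appendix shows otherwise.

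The defence does not cover two things. A reader who follows the pointer finds power for 413 per group, at what matches a 5% level, and nothing for 1752 at any rate. And the claim in 5.1 cannot be reproduced at its own significance level, whatever happened to enrolment later.

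**Conclusion.** The point holds as a reporting error in a power statement on which other documents rely. At 13% and two-sided 2.5%, power is about 84-88% at 2100 and about 76-81% at 1752, against a stated figure above 90%. The appendix's 87.5% corresponds to 80.8% at the plan's level. Safety power for the enrolled number is not stated anywhere. On the appendix's 25% rate it is about 97-99%, so the adequacy of the trial depends on the event rate, with the 90% line at roughly 16% to 18.5%.

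These figures assume an equal split of 1752, full five-year follow-up and proportional hazards. Each range comes from reading 35% as a hazard or a risk reduction. That 2100 and 87.5% both match a two-sided 5% test is an arithmetic match; the documents do not say that this level was used.

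**What to change.** - **Section 3.1:** give 1752 as the number included and operated, in place of 2100 (1050 per group).
- **Section 5.1:** label 2100 as the revised target that followed 4000, and correct its power to about 84-88% at two-sided 2.5%.
- **Section 5.1 or the appendix:** add the safety power at 1752 and two-sided 2.5%, naming the method and saying whether 35% is a hazard or a risk reduction: about 76-81% at a GBP rate of 13%, about 90% at 16-18.5% depending on that choice, and about 97-99% at 25%.
- **Appendix:** restate the 87.5% for 413 per group at the 2.5% level (80.8% by two proportions), and note that 413 comes from weight follow-up.

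The cost is wording only. No patients, data or analyses change; the stated power at 13% becomes less favourable.

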## Appendix:

The unforeseen global Covid-19 pandemic resulted in that almost all elective benign surgery in Scandinavia was cancelled from March 2020. Thus, the pandemic had severe consequences on the recruitment to the BEST trial during 2020-2021.

During autumn of 2021 the BEST steering committee decided to perform an additional analysis of the power for primary endpoints.

Additional information (Courcoulas et al, JAMA Surg 2020 March; Howard et al, JAMA Surg 2021 Dec) revealed that the risk of any of the predefined substantial adverse events after bariatric surgery is higher than previously anticipated in the revised power calculation, i.e. >25% instead of 13%. These figures were confirmed in an analysis of real-world data from the bariatric national quality register SOReg in Sweden which registered all patients undergoing sleeve or bypass in Sweden since 2007.

An independent statistician performed the analysis based on information above, but also on 2-year data in BEST. In conclusion, it was stated:

Two post hoc power analyses were conducted based on the data from February 2022:

*1. Weight reduction. In the protocol the following is stated "This sample size will also have >95% power to evaluate non-inferiority of 5% weight loss difference over 5 years between the two groups, assuming 15 kg standard deviation in weight loss over follow-up with two-sided 2.5% significance level.". The post hoc power calculation is based on the two-year follow up data where an average weight loss for all patients (both groups, N=1031) of 29.3 kg was attained with a Sd=21.6. Given a loss to follow up of 20% from 2 year follow up to the 5-year follow up the sample size is assumed to be  $(1031 \cdot 0.80)/2 = 413$  patients per group. With a non-inferiority level of 5 kg weight loss the power is found to be 90% if  $n=393$  per group, and 95% if  $n=486$  per group (<https://www.sealedenvelope.com/power/continuous-noninferior/>).*

*2. Substantial adverse events. This post hoc power calculation is for a superiority test where the rate is assumed to be 25% for the gastric bypass at 5 years and sleeve would have a 35% lower level, i.e.  $25\% \cdot 0.65 = 16.25\%$ . Given a sample of  $n=413$  per group the post hoc power will then be 87.5%.*

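### The appendix's post hoc powers correspond to a two-sided 5% level, not the two-sided 2.5% the SAP commits to, and section 5.1's adverse-event power falls short of 90% on its own inputs

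*Combined protocol and SAP*

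**What the plan says.** Section 5.2 of the main SAP (version 5) sets the test level: "For primary outcomes, two-sided 2.5% significance level will be used to identify statistically significant results". It adds that "The corresponding confidence intervals to be reported will be 97.5% confidence intervals", and gives the reason: "The use of 2.5% significance is due to two primary endpoints".

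Section 5.1 uses the same level for the design. For the superiority objective, "it is assumed that 13% of patients who undergo GBP will have substantial adverse events" over 5 years, the risk under sleeve gastrectomy (SG) is taken as 35% lower, and 1050 patients per group are said to give ">90% power at two-sided 2.5% significance level using Cox proportional hazards regression model".

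The appendix reports two post hoc calculations:

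- Weight. From two-year data (1031 patients, SD 21.6 kg) and a 20% further loss, it takes 413 patients per group. "With a non-inferiority level of 5 kg weight loss the power is found to be 90" per cent with 393 per group; 95% is given for 486 per group.
- Substantial adverse events. With 25% under gastric bypass (GBP) and 16.25% under SG, "per group the post hoc power will then be 87.5" per cent; the group size is again 413.

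The appendix gives no alpha for either calculation. Item 1 does repeat the protocol's two-sided 2.5% just before its own figures. The text that follows says inclusion was stopped in the light of this information and to avoid prolonging recruitment, with the support of the DSMC, at 1752 patients included and operated.

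**The concern.** The 2.5% level is a split of a 5% error rate over two primary endpoints. Power for either endpoint should therefore use a critical value of 2.241, not 1.960. For non-inferiority, a two-sided 97.5% interval means a one-sided test at 1.25%.

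A reader of the appendix will take its figures to be at the level it has just repeated. If they were computed at the conventional 5%, they describe a more lenient test than the one the trial will run. They are also part of the recorded grounds for an irreversible decision, and they will be consulted again if either primary result is inconclusive.

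**Working it through.** **Critical values.** Two-sided 5% (or one-sided 2.5%): z = 1.960. Two-sided 2.5% (or one-sided 1.25%): z = 2.241. For power, z = 1.282 (90%) and 1.645 (95%).

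**1. Appendix, weight.** Inputs from the appendix: margin 5 kg, SD 21.6 kg. A true difference of zero is assumed, as is usual. Formula: n per group = 2(z_α + z_β)² × SD² / margin².

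- With 1.960: 2 × (1.960 + 1.282)² × 21.6² / 25 = 392.2, rounded up to 393. For 95%: 485.0, rounded up to 486. Both printed figures are reproduced.
- With 2.241: 463.2 → **464**, and 563.7 → **564**.

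Power at n per group is Φ(5 / (21.6 × √(2/n)) − z_α). At n = 413 the first term is 3.326:

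| n per group | z = 1.960 | z = 2.241 |
|---|---|---|
| 393 | 90.1% | 84.2% |
| 413 | 91.4% | **86.1%** |
| 486 | 95.0% | 91.4% |

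**2. Appendix, substantial adverse events.** Inputs: 25% and 16.25%, 413 per group, mean risk 20.625%. Standard error of the difference under the null: √(2 × 0.20625 × 0.79375 / 413) = 0.02816. Under the alternative: √((0.25 × 0.75 + 0.1625 × 0.8375) / 413) = 0.02799.

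- With 1.960: (0.0875 − 1.960 × 0.02816) / 0.02799 = 1.154, so power is 87.6%. The printed 87.5% is reproduced to within 0.1 point.
- With 2.241: (0.0875 − 2.241 × 0.02816) / 0.02799 = 0.871, so power is **80.8%**.

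Other methods at 2.5% do not recover 87.5%: unpooled 81.2%, arcsine 81.1%, continuity-corrected 78.4%, Schoenfeld's formula with hazard ratio ln(0.8375)/ln(0.75) = 0.616, 82.0%.

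**3. Section 5.1, substantial adverse events.** Inputs: 13% in GBP, 0.65 × 13% = 8.45% in SG, 1050 per group. Expected events: 1050 × (0.13 + 0.0845) = 225. Schoenfeld: power = Φ(√(events/4) × |ln HR| − z_α). The 35% reduction can be read as a hazard ratio of 0.65, or as a risk ratio, which gives ln(0.9155)/ln(0.87) = 0.634. The first term is then 3.232 or 3.420.

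| Method | two-sided 5% | two-sided 2.5% |
|---|---|---|
| Schoenfeld, HR 0.65 | 89.8% | 83.9% |
| Schoenfeld, HR 0.634 | 92.8% | 88.1% |
| Freedman, HR 0.65 / 0.634 | 88.9% / 92.0% | 82.7% / 86.9% |
| Two proportions | 92.1% | 87.1% |

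At 2.5%, 90% power needs 239 events (HR 0.634) or 268 (HR 0.65). At an average risk of 10.725%, that is about 2230 or 2500 patients.

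There is a second way to reach the printed figure. If 13% is entered as the event probability for all 2100 patients, there are 273 events. With HR 0.65, √(273/4) × 0.4308 − 2.241 = 1.317, so power is 90.6% at the stated 2.5%, and 268 / 0.13 = 2062 patients suffice for 90%.

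**4. Power at the actual enrolment, two-sided 2.5%.** Assumption: 1752 patients split equally, 876 per group.

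- Adverse events, 25% vs 16.25%, complete follow-up: 98.9% (two proportions), 99.1% (Schoenfeld).
- Adverse events, 13% vs 8.45%: 79.9% (two proportions). With 876 × 0.2145 = 188 events, Schoenfeld gives 76.1% (HR 0.65) to 81.1% (HR 0.634).
- Weight, 5 kg margin, SD 21.6 kg: 99.5% with no loss. With an assumed 20% loss (700 per group), 4.331 − 2.241 = 2.089, so 98.2%. Because 464/876 = 0.53, power stays at 90% or more up to about 47% loss.

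**The case against.** The strongest reply is that nothing of consequence follows. Inclusion has closed, so the 2100 target can no longer be acted on. The figure of 413 is 80% of the 1031 patients with two-year data, halved; it is not the trial's size. SAP section 5.4 expects close to complete adverse-event coverage through registers, and at 876 per group both endpoints have ample power on the appendix assumptions. The stop also had another stated reason, not prolonging recruitment. All of that stands, and it limits the consequence. It does not make the printed figures right for the test in section 5.2.

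A second reply concerns section 5.1: the figure above 90% can be obtained at 2.5% with 273 events. That is so, and the documents do not say how the calculation was done. A reader might infer that every power figure in the SAP was computed at 5%, but section 5.1 does not support this. The route through 273 events does conflict with the section's own wording, which assigns 13% to GBP patients and a lower risk to SG. The power is therefore overstated for the inputs as written; only the cause is open.

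The section 5.1 weight figure (90%, SD 15 kg) does not fit the pattern either. With a 5 kg margin and 1050 per group, power exceeds 99.99% at either level, so 90% would be understated. Its difficulty is a percentage margin set against an SD in kilograms, which is a separate matter.

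**Conclusion.** The concern holds for the appendix and, with its cause left open, for the adverse-event power in section 5.1.

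- The appendix does not name its alpha, so the 5% level is inferred. The inference is firm: 393 and 486 are matched exactly and 87.5% to within 0.1 point, and none is matched at 2.5%.
- At the committed level, power at 413 per group is about 5 points lower for weight (86% against 91%) and about 7 points lower for adverse events (81% against 87.5%).
- The section 5.1 adverse-event power is 2 to 7 points below 90%, depending on the method and on whether 35% is a risk or a hazard reduction.

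A reader might go further and conclude that the trial is underpowered. The documents do not support that on the appendix assumptions, given the 1752 enrolled. The weaker case is the 13% rate of section 5.1, where power at 876 per group is about 80%; the appendix itself regards that rate as too low. Nor is the primary analysis affected: the tests, the 2.5% level and the 97.5% intervals in section 5.2 are sound as they stand. What needs correcting is the reported power.

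**What to change.** In the appendix and in section 5.1:

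- State the alpha and sidedness of each power calculation.
- Restate the appendix weight figures at two-sided 2.5%: 464 and 564 per group for 90% and 95% power, and 86% at 413.
- Restate the appendix adverse-event power at 413 per group as about 81%.
- Restate the section 5.1 adverse-event power as about 83–88% for 13% vs 8.45% with 1050 per group. If 13% was meant as the overall event rate, say so and correct the input instead.
- Add power at the 1752 enrolled, with the real group sizes and expected follow-up. On an equal split this is about 99% for adverse events at 25% vs 16.25%, about 80% at 13% vs 8.45%, and about 98% for weight after an assumed 20% loss.

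The cost is a few lines of SAP text and some less favourable numbers at 413 per group. No patients, data or changes to the primary analysis are needed.

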## 2. Study objectives

The objective of the study is to evaluate the safety and effectiveness of SG compared to GBP in obese patients eligible for bariatric surgery.

The study has two primary objectives, evaluating superiority and non-inferiority. The study hypothesis for superiority is that patients treated with SG will experience fewer adverse events during the 5-year follow-up as compared to patients treated with GBP.

For non-inferiority, the study hypothesis is that the weight loss in the SG group, as compared to GBP, is within a non-inferiority margin of 5% at 5 years after surgery.

Secondary objectives of the study include health economics, inpatient hospital and outpatient care, drug consumption, alcohol abuse, fractures and bone quality, diabetes, cancer, mortality, and quality of life.

Predefined subgroup analyses will be done by sex, age, diabetes status and body mass index (BMI).

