## 4. Study outcomes

A list of substantial adverse events in bariatric surgery (tabl 2) was predefined before study start. Possible occurrence of any of these will be identified in the CRF (SOREg) but additionally from the national quality health care registries (listed above) during 5-years of follow-up. A superiority of SG over GBP would require >35% fewer patients experiencing one or more substantial adverse event.

Time to occurrence of first substantial adverse event will be analysed as the co-primary outcome. Patients will be defined as either having or not having an event, and thus the number of events in the same patients will not be summarized.

For non-inferiority, weight loss difference over 5-years in patients operated with SG as compared to GBP will be evaluated with regards to the non-inferiority margin of 5%.

Table 1: Primary outcomes:

| Outcome                    | Time frame                  | Explanation                                                                          |
|----------------------------|-----------------------------|--------------------------------------------------------------------------------------|
| Weight loss                | At 5 years after surgery    | Change in weight from baseline in % of total body weight                             |
| Substantial adverse events | Over 5 years after surgery. | Number of patients with any substantial adverse events defined according to table 2. |

Table 2: Substantial adverse events: (events that may have a significant and/or longstanding effect on patients' health and/or everyday life).

| Substantial adverse event              |                                                                                                                                                                                                                                                                                               |
|----------------------------------------|-----------------------------------------------------------------------------------------------------------------------------------------------------------------------------------------------------------------------------------------------------------------------------------------------|

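### The 90% power that SAP 5.1 states for weight non-inferiority does not reproduce from inputs in the documents at zero true difference, and the appendix calculation does not settle it

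*Combined protocol and SAP*

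**What the plan says.** SAP section 5.1 sizes the trial on adverse events ("1050 in each group) will be required to detect a difference in time to substantial adverse event with" more than 90% power) and then adds the weight outcome: "This sample size will also have 90% power to evaluate non-inferiority of 5 % weight loss difference". The only spread given is "assuming 15 kg standard deviation in weight loss over follow"-up, and the level is two-sided 2.5%. Section 5.2 confirms that level: "For primary outcomes, two-sided 2.5% significance level will be used to identify statistically significant results".

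The margin appears in three forms. Section 2 says that the weight loss with sleeve gastrectomy (SG) "is within a non-inferiority margin of 5% at 5 years after surgery", without saying what the 5% is a percentage of. Table 1 in section 4 defines the outcome as "Change in weight from baseline in % of total body weight". Item 1 of the appendix calculates with 5 kg.

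Section 5.1 refers the reader to the appendix for an updated calculation. The appendix begins by quoting the protocol's power sentence as "This sample size will also have >95% power to evaluate non-inferiority of 5% weight loss difference over 5 years between the two groups". It then reports two-year data, "an average weight loss for all patients (both groups, N=1031) of 29.3 kg was attained with a Sd=21.6", and allows 20% further loss to reach 413 per group. It gives 393 per group for 90% power and 486 for 95%. Inclusion stopped at 1752 patients.

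**The concern.** A stated power should follow from the inputs printed beside it. Here 90% looked too low for a margin of 5 kg or more with 1050 per group, and too high for a margin of 5% of the weight lost. Section 5.1 gives no base for the percentage, no expected weight loss, no true difference and no allowance for missing weights, so a reader cannot rebuild the number.

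Weight non-inferiority is one of two primary outcomes, and the appendix calculation informed the decision to stop inclusion. If neither calculation matches the planned test, the SAP holds no power figure for this outcome that can be cited with the result.

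**Working it through.** **Inputs from the documents.** 1050 per group, SD 15 kg, two-sided 2.5% (5.1 and 5.2); mean two-year loss 29.3 kg, pooled SD 21.6 kg, margin 5 kg, 413 per group (appendix); 1752 enrolled (appendix).

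**Assumptions.** Normal approximation and 1:1 allocation. True difference d = 0 unless stated. Baseline weight 120 kg, which the documents do not give. At an assumed height of 1.68 m, the BMI range 35–50 spans about 99–141 kg, so 5% of body weight is about 5–7 kg.

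**Formulas.**
- SE = SD × √(2/n)
- Power = Φ((margin − d)/SE − z)
- n per group = 2 × SD² × (z + z_power)² / margin²

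A two-sided 2.5% level puts 0.0125 in the tail that matters, so z = 2.241. For one-sided 2.5%, z = 1.960. For 90% and 95% power, z_power = 1.282 and 1.645.

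**Step 1: the 90% in section 5.1.** SE = 15 × √(2/1050) = 0.6547 kg.

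| Reading of 5% | Margin | Margin/SE | Power, two-sided 2.5% |
|---|---|---|---|
| 5 kg (appendix) | 5 kg | 7.64 | >99.99% |
| 5% of body weight, 120 kg assumed | 6 kg | 9.17 | >99.99% |
| 5% of the 29.3 kg loss | 1.465 kg | 2.24 | 49.9% |

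One-sided 2.5% raises the last row only to 60.9%. Losing 20% of patients (840 per group) leaves 5 kg above 99.99% and lowers the last row to 40.5%.

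**Step 2: what would give 90%.**
- The margin would be (2.241 + 1.282) × 0.6547 = 2.31 kg. As 5% of the loss, that implies a mean loss of 2.31/0.05 ≈ 46 kg.
- With a 5 kg margin, the true SG deficit would be 5 − 2.31 ≈ 2.7 kg.
- With a 5 kg margin and d = 0, only 224 per group would be needed: 2 × 15² × 3.523²/5² = 223.4.

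None of these values is in the documents.

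**Step 3: the SD.** The variance ratio is (21.6/15)² = 2.07. At 1050 per group and a 5 kg margin, SD 21.6 gives SE 0.943 kg and power 99.9%. On the 1.465 kg reading, power falls from 49.9% to 24.6%.

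**Step 4: the appendix figures (5 kg, SD 21.6).**

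| Level | n for 90% | n for 95% | Power at 413 per group |
|---|---|---|---|
| One-sided 2.5% | 392.2 → 393 | 485.0 → 486 | 91.4% |
| Two-sided 2.5% (SAP 5.1, 5.2) | 463.2 → 464 | 563.7 → 564 | 86.1% |

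The appendix's numbers reproduce exactly, but at one-sided 2.5%.

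**Step 5: final enrolment.** 1752/2 = 876 per group; margin 5 kg, SD 21.6, two-sided 2.5%. The retention rates are assumptions.

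| Retention | n per group | d = 0 | SG deficit 1 kg | SG deficit 2 kg |
|---|---|---|---|---|
| 100% | 876 | 99.5% | – | – |
| 80% | 701 | 98.2% | 89.0% | 64.0% |
| 60% | 526 | 93.5% | 77.7% | 50.4% |

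**The case against.** The strongest reply is that 90% is safe. On the two readings that the documents themselves use, kg in the appendix and percent of body weight in Table 1, power at zero difference is far above 90%. The appendix's >95% is then true as well. This stands: on those readings 5.1 understates the power. It does not make 90% the result of the stated inputs. A few lines earlier, 5.1 writes the adverse-event power as greater than 90%, so a floor was marked where one was meant.

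A second reply is that 5.1 does not state a true difference, and that the protocol's background expects somewhat smaller effects after SG. A deficit near 2.7 kg would give 90% with a 5 kg margin. Likewise, an expected loss of about 46 kg would give 90% if the margin is 5% of the loss. This also stands. It shows an under-specified calculation and rules out saying that no reading could produce 90%.

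A third reply is that the SD is already dealt with, because 5.1 points to an appendix that reports and uses 21.6 kg. That is fair. A reader might infer that the trial's data refute the 15 kg assumption and that this breaks the power claim. The documents do not support that. The 21.6 kg is a two-year value pooled over both groups, not a five-year within-group SD, and at 1050 per group with a 5 kg margin it still leaves 99.9%. What remains is that the appendix calculation uses a different level from the planned test.

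Finally, inclusion has closed and the sentence changes no analysis. True, so this is a correction to the record and not to the design.

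**Conclusion.** The 90% in SAP 5.1 does not reproduce from inputs in the documents when the true difference is zero. Power is above 99.99% for a margin of 5 kg or 5% of body weight (baseline weight assumed), and about 50% for 5% of the 29.3 kg two-year loss. The main cause is a margin without a stated base and unit, together with an unstated true difference. The 90% in 5.1 and the >95% quoted in the appendix do not match, although >95% holds on the kg and body-weight readings.

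The appendix does not settle the matter. At the SAP's two-sided 2.5% its targets become 464 and 564 per group, and its 413 per group gives 86.1%.

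A reader might conclude that the weight comparison is underpowered or near a coin toss. The documents do not show this. The 50% figure arises only if the margin is 5% of the loss, a reading that no calculation in the SAP uses. With 1752 enrolled, a 5 kg margin and zero true difference, power stays above 90% at either assumed retention rate. It is sensitive to a true SG deficit, which no power statement mentions.

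**What to change.** Restate the weight power in 5.1 and the appendix as one calculation that a reader can repeat. It should state:

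- the margin with its base and unit, exactly as it will be tested;
- SD 21.6 kg, labelled as a pooled two-year value, or its equivalent in percent of body weight;
- the two-sided 2.5% level;
- 1752 enrolled and an explicit five-year weight retention;
- the assumed true difference, with at least one non-zero SG deficit shown beside zero.

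For a 5 kg margin, the entries would be about 98% (80% retention) and 93.5% (60%) at zero difference, and about 89% and 78% with a 1 kg SG deficit. The appendix's 393 and 486 should be replaced by 464 and 564, or labelled as one-sided 2.5%. Keep the >95% sentence as a quotation of earlier text, marked as superseded.

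The cost is SAP wording and one recalculation. No data collection or planned analysis changes.
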